### Baseline data collection

Upon consent, study participants complete a baseline survey composed of items measuring their health behaviors (including self-reported adherence, physical activity, and diet), psychosocial attributes (e.g., depressive symptomology, hypertension-related locus of control, and adaptive stress management techniques), perceived health status, and healthcare utilization.

Baseline measures of BP, waist circumference, height, and weight are also obtained. Blood pressure is assessed using a digital Omron 10 series device. Women are seated at rest for 5 min with their feet flat on the floor, and their arms raised at the heart level. Appropriate cuff sizes, based on each participant’s arm circumference, are attached to the device to detect their BP reading accurately.

### PTSC intervention

Members of the intervention group meet once a week over a 13-week period. During the first two-hour session, women learn about the program and discuss administrative details. In the remaining the Sister Circle sessions, facilitators and/or experts provide interactive educational presentations on topics related to high blood pressure and its management. These topics include stress management, inflammation, hypertension, and heart disease; depression and anxiety; self-esteem; physical activity and nutrition; strategies to partner with health care team members; and psychosocial issues unique to AA midlife women. Facilitators elicit participants’ challenges and successes from the previous week and use them as the basis for role-playing activities. This allows the women in the Sister Circle to work through specific scenarios based on the intersection of their personal circumstances and their attempts to adopt healthier behaviors.

Participants are also taught to accurately measure, record, and monitor their weight, body-mass-index (BMI), abdominal circumference, and blood pressure. They complete daily diaries and journals to log their behaviors and track their progress on achieving their health management goals. Participants receive $10 at each session to assist with transportation. They also receive the book, *Prime Time: The African American Woman’s Complete Guide to Midlife Health and Wellness,* [26] written by the co-developers of the PTSC Program, and relevant educational articles, self-assessments, home BP monitors, and pedometers. Upon completion of the PTSC program, participants officially graduate and obtain a certificate of completion from GPHIC, and a certificate of congratulations and gift from JHCHDS.

### Follow-up data collection

Follow-up surveys are completed at 13 weeks (end of the intervention), 9 months (6 months after the end of the intervention), and 15 months (a year after the end of the intervention). At the 15-month mark, those in the control group are eligible to enroll in the standard PTSC program. Study participants receive a $50 gift card each time they attend a data collection session. Participants who attend the recruitment session and all three follow-up sessions receive a total of $200. Administrative records from Unity are used to track healthcare utilization and costs over the study period. Thus far, two cohorts have enrolled in the study.

### Primary and secondary outcomes

The study’s primary outcomes are changes in blood pressure (baseline compared to 1-month post-intervention, 6 months post-intervention, and 1-year post-intervention); hospital utilization and admission, as well as emergency department utilization, attributable to cardiovascular events (obtained from Unity’s and BMSI’s medical records), and the intervention’s return on investment (which entails an interpolation of values from reported utilization from hospitalizations and ER, and lab and pharmacy visits, from Unity and BMSI). The secondary outcomes include changes in weight, BMI, and waist circumference; knowledge of causes and consequences of high blood pressure; hypertension-related locus of control; stress management techniques; self-reported physical activity, dietary behaviors, and blood pressure monitoring; and medication adherence. Data collection occurring at baseline, 13 weeks, 9 months, and 15 months post-intervention will capture blood pressure, weight, BMI, waist circumference, and the aforementioned secondary outcomes.

To assess participants’ knowledge about hypertension causes and consequences, we use the CAATCH Hypertension Knowledge Questionnaire, a 17-item questionnaire that requires to respondents to indicate if statements related to hypertension sequalae are true or false and is a modified version of a hypertension knowledge questionnaire developed by the National Heart, Lung, and Blood Institute [27, 28]. We measure hypertension-related locus of control, defined as a person’s beliefs concerning where control over their health lies, by modifying Form C of the Multidimensional Locus of Control Scale (specifically, we replaced “health” with. “hypertension” in each of the items) [29]. Stress management techniques are measured through a set of questions asking participants to report whether or not they are doing anything to lower their stress. If participants indicate “yes,” they are asked to mark which strategies they have employed to do so (all that apply). Responses include “listen to music or relaxation tapes,” “avoid it/forget about it,” “do yoga or tai chi,” and “talk with professional counselor or therapist.” Self-reported physical activity is evaluated through questions asking whether or not participants engaged in at least 30 min of exercise during the week. If they answered “yes,” they were asked to indicate what type(s) of exercises they did (e.g., walking, dancing, swimming). We elicit dietary behaviors through questions that asked how participants eat in a typical day; participants indicated whether or not they did such things as adding salt to their food, consuming fast food, or eating when they are upset. Blood pressure self-monitoring is encapsulated through questions that asked whether or not participants have taken their own blood in the last 12 months and, if so, if they have done so daily, weekly, or monthly. Finally, medication adherence is measured through the 9-item Hill-Bone Medication Adherence scale [30]. Scores range from 9 to 36, with higher scores reflecting poorer adherence to antihypertensive pharmacological therapies [31].

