### Hypotheses

We hypothesize that patients randomized to PTSC will have better-controlled blood pressure than patients who receive usual care at the end of the intervention (13 weeks) and up to one-year post-intervention (15 months). We expect patients randomized to the PTSC intervention to demonstrate a more significant increase in health knowledge, hypertension-related locus of control, physical activity, medication adherence, and stress management practices than patients receiving usual care. Finally, we anticipate that patients randomized to PTSC will have fewer hospitalizations and emergency rooms visits for cardiovascular-related events than patients receiving usual care, and that the costs of providing PTSC will be offset by reductions in healthcare costs associated with health improvements for patients randomized to PTSC, compared to patients receiving usual care.

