### Power calculation

In order to detect a statistically significant difference in blood pressure control between the intervention and control groups post-exposure to the PTSC intervention, we need 440 participants (*n* = 220 per group) in our study. Our power calculations were based on the assumption of 80% HTN prevalence among study participants in both treatment arms at baseline, a two-sided alpha of 0.05, and a 15% reduction in the proportion of participants with high blood pressure after receipt of the PTSC intervention. The calculated sample size was 308, but our experience developing, implementing, and evaluating interventions with this target population suggests that we should anticipate a relatively high attrition rate. Thus, we computed a potential attrition rate of roughly 40%. In order to have sufficient power to detect a 15% reduction in HTN in the intervention group, we will recruit at least 40% above the estimated sample size, for a total sample size of 440 participants between Unity and BMSI health systems.

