### Analysis plan

Study data will be exported into Stata 15 for statistical analysis. We will set statistical significance at *p* ≤ 0.05. Baseline descriptive characteristics and outcomes will be analyzed using mean and standard deviation (SD) for continuous data, and counts and percentages for categorical data**.** We will conduct unequal variances t-tests in order to detect statistically significant differences between the treatment arms. To assess the impact of the PTSC program on participants’ blood pressure, weight, BMI, waist circumference, and all of the secondary outcomes, we will employ a difference-in-differences methodology to observe changes in participants’ outcomes at 3 months, 6 months, and 12 months post-intervention. We will also use multivariable regression analyses to discern whether or not participants’ outcomes improved as a result of receiving the PTSC intervention. Our models will control for patients’ sociodemographic characteristics (including age, marital status, and income), health insurance status, substance use (namely, smoking and drinking), and the presence of chronic conditions.

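### Blood pressure, cardiovascular hospital use, emergency use and return on investment are all primary with no deciding endpoint named; if any one may carry the claim, the false-positive rate is about 8-19%, not 5%

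*Protocol article*

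**What the plan says.** The section on primary and secondary outcomes opens with "The study’s primary outcomes are changes in blood pressure (baseline compared to 1-month post-intervention, 6 months post-intervention, and 1-year post-intervention". It continues the same list with "hospital utilization and admission, as well as emergency department utilization, attributable to cardiovascular events", and then "and the intervention’s return on investment". No order is given, and no rule says which outcome, or how many, must succeed.

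Other sections bear on how these outcomes would be used:

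- **Study design** sets separate aims for blood pressure control and for testing a cost offset.
- **Hypotheses** gives blood pressure, utilization and cost a directional statement each. For utilization it expects "fewer hospitalizations and emergency rooms visits for cardiovascular-related events than patients receiving usual care".
- **Power calculation** seeks enough participants to "detect a statistically significant difference in blood pressure control between the intervention and control groups", with "a two-sided alpha of 0.05". No other outcome is sized.
- **Analysis plan** says "We will set statistical significance at *p* ≤ 0.05" as a general statement. Blood pressure is the only primary outcome it names for the difference-in-differences analysis. It names no test for utilization or return on investment.

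**The concern.** The primary outcomes can disagree. Blood pressure could show no difference while emergency use or return on investment falls below 0.05. As written, nothing in the article stops such a result from being reported as a positive primary finding. In that case the two-sided 0.05 behind the sample size is not the trial's false-positive rate.

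A null blood pressure result is a real possibility. The Discussion reports that 103 of 216 women assigned to the programme received it as designed, and it recognises that this threatens the ability to detect differences. An outcome for which the trial was not sized could then become the headline.

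**Working it through.** **Step 1: which endpoint the sample size rests on.** Inputs from the power calculation are 80% with high blood pressure at baseline, a 15% reduction, two-sided 0.05 and a stated total of 308 before attrition. Power is not given as a number. The reduction is read as absolute, 80% to 65%.

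n per arm = [1.96·√(2·0.725·0.275) + z_power·√(0.8·0.2 + 0.65·0.35)]² / 0.15²

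- 80% power: 138 per arm, 276 in total. With continuity correction: 151 per arm, 302 in total.
- 85% power, no correction: 158 per arm, 316 in total.

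The stated 308 lies between 302 and 316, within 3% of each. A relative reduction (80% to 68%) needs 418 to 450 at 80% power and does not fit. So 308 is approximately reproduced as a single comparison of blood pressure control at an undivided 0.05.

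**Step 2: how many primary tests.** The article leaves this open, so three counts are used, each with blood pressure at one visit:

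- Four: blood pressure, hospital use, emergency use, return on investment.
- Three: hospital and emergency use merged (they share one clause), or return on investment only estimated.
- Two: both of these simplifications together.

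**Step 3: chance of at least one false positive, all nulls true, each test two-sided 0.05.** For independent tests it is 1 − 0.95^k. For a common correlation r between the test statistics, with c = 1.96, it is

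1 − ∫ φ(x)·[Φ((c − √r·x)/√(1−r)) − Φ((−c − √r·x)/√(1−r))]^k dx

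The correlation is an assumption, because the article gives none.

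| Tests | r = 0 | r = 0.3 | r = 0.5 | r = 0.8 |
|---|---|---|---|---|
| 4 | 18.5% | 17.4% | 15.6% | 11.4% |
| 3 | 14.3% | 13.6% | 12.5% | 9.8% |
| 2 | 9.75% | 9.5% | 9.1% | 7.8% |

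Return on investment is built partly from hospital and emergency use, so a common r of 0 across all four is unlikely. With blood pressure independent and the other three correlated at 0.5 to 0.9, the rate is 16.9% to 12.9%.

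**Step 4: blood pressure not significant, another primary significant.** Under the global null with four tests, this is the figure in Step 3 minus the 5% for blood pressure itself:

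- r = 0: 18.5% − 5% = 13.5%
- r = 0.5: 15.6% − 5% = 10.6%
- r = 0.8: 11.4% − 5% = 6.4%

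**Step 5: false claims in favour of the programme only.** With four tests this is 1 − 0.975⁴ = 9.6% at r = 0, 7.8% at r = 0.5 and 5.7% at r = 0.8. The reference for a single test is 2.5%.

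**Step 6: blood pressure visits.** The outcomes section lists three follow-up comparisons. Three visits each at 0.05 give the three-test row, 14.3% to 9.8%. Naming blood pressure as the sole primary without naming a visit would therefore not restore 5%.

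**The case against.** This is a journal article and the analysis plan is not shown. A multiplicity procedure is commonly left to that plan, so its absence here is not an error. That stands, and the point does not rest on it. It rests on what the article does fix: several outcomes labelled primary without rank, beside a sample size for only one of them.

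A reader might infer that every primary outcome will be tested at 0.05. The document does not support this. The threshold is general, no test is described for utilization or return on investment, and the latter reads largely as an economic estimate. On the other side, the study aims speak of testing a cost offset, and the hypotheses cover both utilization and cost. The number of tests is therefore open, which is why the range extends down to two.

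A reader might also infer that the plan declares success on any single outcome. No sentence says so. The aims are separate, and whether error control across separate aims is required is debated. Blood pressure control is the first aim, the first hypothesis and the only sized endpoint, so the leading endpoint is signalled. It is still not named as the one that decides.

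**Conclusion.** The concern holds in a conditional form. The article does not identify the outcome that decides the trial. If any one significant primary outcome may support a positive claim, the false-positive rate at a single blood pressure visit is about 8-19% instead of 5%. The width of that range comes from two things the article leaves open: the number of tests (four, three or two) and the correlation (assumed 0 to 0.8). With four tests and no true effect, the chance that blood pressure fails while another primary outcome succeeds is about 6-14%.

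The 11-19% for four tests should not be quoted as the trial's error rate. It is the upper part of the range and holds only if all four outcomes are formally tested. Even the lowest figure, 7.8%, is above 5%, so the point is worth correcting.

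**What to change.** In the outcomes section, name blood pressure control, the endpoint that was sized, at one stated follow-up visit as the single deciding primary outcome at two-sided 0.05. State openly that this replaces change in blood pressure as the deciding measure. The visit should be one that is actually scheduled: the outcomes section refers to one month post-intervention, whereas the follow-up section lists 13 weeks, 9 months and 15 months.

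Make the other blood pressure visits, cardiovascular hospital use, emergency use and return on investment key secondary. Either test them in a pre-stated order, only after the primary succeeds, or report them as estimates with confidence intervals and no significance claim. The order is the sponsor's choice. If the sponsor wants four co-equal primary outcomes instead, a Bonferroni split gives 0.05/4 = 0.0125 each, which blood pressure control was not sized for.

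The single-primary fix needs no new data and leaves the planned power for blood pressure control unchanged. It has two costs. Utilization and return on investment can no longer carry a stand-alone primary claim, for which the trial was not sized. It also changes the primary outcomes mid-trial, with 341 women already recruited and a registry entry in place. It must therefore be dated, justified and entered in the registry before any outcome data are compared by arm. The article describes preliminary analyses only of baseline characteristics, programme attendance and attrition, so this still appears possible.

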### Analysis plan

Study data will be exported into Stata 15 for statistical analysis. We will set statistical significance at *p* ≤ 0.05. Baseline descriptive characteristics and outcomes will be analyzed using mean and standard deviation (SD) for continuous data, and counts and percentages for categorical data**.** We will conduct unequal variances t-tests in order to detect statistically significant differences between the treatment arms. To assess the impact of the PTSC program on participants’ blood pressure, weight, BMI, waist circumference, and all of the secondary outcomes, we will employ a difference-in-differences methodology to observe changes in participants’ outcomes at 3 months, 6 months, and 12 months post-intervention. We will also use multivariable regression analyses to discern whether or not participants’ outcomes improved as a result of receiving the PTSC intervention. Our models will control for patients’ sociodemographic characteristics (including age, marital status, and income), health insurance status, substance use (namely, smoking and drinking), and the presence of chronic conditions.

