### PTSC program overview

The PTSC Program is a multifaceted, theoretically-driven, community-based peer support intervention targeting AA women who are 40 to 75 years of age. It was developed by two mid-life AA women, Drs. [name], a physician, and [name], a clinical psychologist, and established through the auspices of The Gaston and Porter Health Improvement Center, Inc. (GPHIC). The GPHIC’s National Training Institute trains PTSC facilitators on cardiovascular conditions, group facilitation and leadership skills, and the cultural beliefs undergirding self-management of chronic conditions. The facilitators are PTSC program graduates who live in the communities served by the program.

The PTSC program occurs over 13 weeks. Each facilitator-led Sister Circle includes 25 to 30 women. Each session lasts for 2 h and are held in accessible community sites (e.g., churches, public housing). Sister Circles are characterized by didactic training, guided discussions, and role-playing exercises that address CVD risk factors and strategies to overcome them. Facilitators follow a curriculum designed by the GPHIC that complies with The National Standards for Culturally and Linguistically Appropriate Services in Health and Health Care [17, 18]. The curriculum and its associated materials use text and illustrations to enhance knowledge uptake among women with varying literacy levels.

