The PTSC Program draws from three theoretical frameworks: the social cognitive theory [19], the transtheoretical model [20], and the Person, Extended Family, Neighborhood model [21]. Constructs from these models influence the PTSC Program’s underlying theory of change: by convening women in supportive Sister Circles led by a racially and socioeconomically concordant facilitator, participants will engage in peer learning and will initiate and maintain relationships with women in their community who are embarking on similar health journeys. This will lead to 1) improved knowledge, attitudes, and beliefs about hypertension and cardiovascular disease risk management, 2) improved self-efficacy related to adherence to pharmacological and lifestyle-based antihypertensive regimens, 3) individual, familial, and community capacity around hypertension prevention or management, and 4) improved blood pressure management among mid-life Black women, thereby reducing seemingly intransigent disparities observed within this population (explicated in Fig. 3). Its conceptual roots are consistent with empirical work documenting the importance of social support and social circles in promoting positive health changes among AA women [22–24].

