### Recruitment and randomization

Recruitment procedures commenced in 2017 and will cease in 2022. In the first wave of recruitment, Unity Health Care generated a list of the names and addresses of patients across their practices who fulfilled the study’s eligibility criteria. Candidate participants received a letter describing the study, incentives for participation, contact information for whom to follow up with, and the dates and locations for the recruitment sessions. We have also relied on word-of-mouth and targeted recruitment at Unity’s practices: Unity providers supplemented recruitment efforts by handing out flyers to eligible patients. We will follow the same recruitment processes for our BMSI participants.

Recruitment sessions, which occur in both the morning and afternoon of the same day to maximize attendance, are held in local churches located in predominantly AA neighborhoods. Women are randomly assigned to attend a session designed for the treatment arm or the usual care arm. JHCHDS staff, who conduct the randomization, are blinded to which sessions are for either arm, and both receive identical recruitment sessions. Each session features two interactive presentations. The first presentation, conducted by the GPHIC, describes cardiovascular health disparities at large and the ramifications of hypertension within AA communities, and highlights core components of the PTSC program. The second presentation, given by the JHCHDS, explains the study’s goals, timelines, and data collection procedures, and walks participants through the informed consent process. Attendees learn of their assigned treatment arm after the presentations have been made. At that point, written consent to participate in the study is obtained from those who wish to be a part of the trial.

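### The PTSC arm is treated in circles of 25 to 30 women, but neither the sample size nor the analysis plan names an allowance for clustering within circles

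*Protocol article*

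**What the plan says.** Randomisation is by woman (Recruitment and randomization): "Women are randomly assigned to attend a session designed for the treatment arm or the usual care arm". The intervention is delivered in groups (PTSC program overview): "Each facilitator-led Sister Circle includes 25 to 30 women". The groups are long-lived (PTSC intervention): "Members of the intervention group meet once a week over a 13-week period". The theory of change in the program overview relies on the group: "participants will engage in peer learning and will initiate and maintain relationships with women in their community". No grouping is described for usual care.

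The Power calculation section rests on "the assumption of 80% HTN prevalence among study participants in both treatment arms at baseline", "a two-sided alpha of 0.05", a 15% reduction in the proportion with high blood pressure, and roughly 40% attrition. It reports that "The calculated sample size was 308" and raises this to 440, giving attrition as the only reason. It mentions no ICC, design effect or number of circles.

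The Analysis plan states: "We will conduct unequal variances t-tests in order to detect statistically significant differences between the treatment arms". It then names difference-in-differences and multivariable regression. The listed covariates are all patient-level (sociodemographics, insurance, substance use, chronic conditions). Circle and facilitator do not appear.

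**The concern.** Women who spend 13 weekly sessions with the same facilitator and peers may come to have correlated outcomes. For this programme that is part of the intended mechanism. The correlation arises in one arm only, so the variance of the PTSC mean is larger than a calculation on independent women gives, while the usual-care variance is unchanged.

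An analysis that ignores this produces intervals that are too narrow and rejects a true null hypothesis more often than the 5% set in the Analysis plan. The error leans towards declaring the programme effective. It reaches blood pressure, a primary outcome, and any other between-arm comparison after baseline that is analysed in the same way. A sample size derived for independent women also gives less power than that derivation implies.

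**Working it through.** **Inputs from the protocol article.** Circle size m is 25 to 30 (midpoint 27.5). The high blood pressure proportion is 80%, taken to persist in usual care. A 15% reduction gives 65% if absolute, or 0.80 × 0.85 = 68% if relative. Alpha is two-sided 0.05. Evaluable size is 308, or 154 per arm; planned recruitment is 440, or 220 per arm. Recruitment so far is 216:125, with about 100 more women to come from Baltimore. Of the 216, 103 attended at least 8 of 13 sessions.

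**Assumptions.** The ICC is not given; 0.01 to 0.05 is used. Power is not stated either, so 80% and 85% are tried.

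**Step 1: where 308 comes from.** Independent-samples formula for 80% vs 65%, 1:1:
- 80% power, pooled variance: 138 per arm, 276 in total
- 80% power with continuity correction: 151 per arm, 302 in total
- 85% power, unpooled: 155 per arm, 310 in total
- 85% power, pooled: 158 per arm, 316 in total

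The last three lie within 3% of 308; none equals it. The relative reading (68%) needs 418 at 80% power and does not fit. So 308 is close to a calculation for independent women and needs no design effect to explain it. The step to 440 equals 308 / 0.70, which leaves no separate reserve for clustering.

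**Step 2: formulas for clustering in one arm.**
- Design effect in the PTSC arm: DE = 1 + (m − 1) × ICC
- Power = Φ(0.15 / SE − 1.96), with SE² = 0.80 × 0.20 / n_C + DE × 0.65 × 0.35 / n_I
- Type I error if circles are ignored = 2 × [1 − Φ(1.96 / √R)], with R = (1/n_C + DE/n_I) / (1/n_C + 1/n_I). For equal arms R = (1 + DE) / 2.

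**Step 3: 154 per arm, m = 27.5.** At ICC 0, SE² = (0.16 + 0.2275) / 154 = 0.00252, SE = 0.0502 and power = Φ(1.03) = 85%.

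| ICC | DE | √R | Type I error if ignored | Power allowing for circles |
|---|---|---|---|---|
| 0 | 1.00 | 1.00 | 5.0% | 85% |
| 0.01 | 1.27 | 1.06 | 6.6% | 79% |
| 0.02 | 1.53 | 1.12 | 8.1% | 74% |
| 0.05 | 2.33 | 1.29 | 12.8% | 61% |

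With pooled variance under the null hypothesis, the power column reads 84%, 79%, 74% and 63%.

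**Step 4: unequal arms.** If Baltimore's 100 women split evenly (an assumption), the arms are 216 + 50 = 266 and 125 + 50 = 175. The PTSC arm's share of the naive variance is 175 / 441 = 0.397, so R = 1 + 0.397 × (DE − 1) = 1.105 to 1.526. Type I error is 6.2% to 11.3%.

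**Step 5: low attendance.** Suppose only the 103 of 216 regular attenders share a circle effect. Then DE = 1 + 26.5 × (103/216)² × ICC = 1 + 6.03 × ICC, which is 1.06 to 1.30. At 154 per arm, type I error is 5.3% to 6.8% and power 84% to 79%.

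**Step 6: number of circles.** 220 / 30 = 7.3 and 220 / 25 = 8.8; 266 / 30 = 8.9 and 266 / 25 = 10.6. About 7 to 11 circles carry the PTSC arm, too few for cluster-robust errors without a small-sample correction.

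**The case against.** Four points on the other side deserve weight.

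- **The t-test sentence may concern baseline.** It directly follows a sentence on baseline descriptives, and the effect analyses come after it. Before the circles have met they cannot have induced correlation, so a baseline-only t-test would be harmless in this respect. This stands as a possible reading, and the fix is therefore limited to comparisons after baseline.
- **The article is silent on standard errors for difference-in-differences and regression.** Both methods can carry cluster-robust errors or random effects, and a fuller document not shown here may specify them. This stands. A reader might infer that all three analyses definitely treat women as independent. The text supports only that no circle term is named and that the listed covariates are patient-level. A later analysis document could not, however, put a design effect into the calculation that gave 308.
- **No power figure is stated.** A reader might say that the plan overstates its power. The article promises only sufficient power; the 85% starting point comes from Step 3 above. The supportable statement is that 308 yields less than an unclustered calculation implies.
- **Many women hardly attended.** The Discussion reports that most attrition occurred before the first session, and women who never sat in a circle cannot acquire its correlation. This is a strong argument on size. It lowers the upper type I figure from 12.8% to 6.8% in the extreme case of Step 5, but it does not remove the error. Some of the other 113 women may have attended a few sessions, so the truth could lie between the two scenarios.

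The Discussion also says that third-cohort women will choose a daytime, evening or weekend circle. That this makes circle members more alike is plausible, but the article does not show it, and no figure here depends on it.

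**Conclusion.** The point holds in a limited form. The partially nested structure is plain from the article. The sample-size inputs include no clustering allowance, and the Analysis plan names no circle term. If circles are ignored and the intra-circle correlation is positive, the direction is clear: standard errors are too small, type I error exceeds 5%, and power is below that of an unclustered calculation.

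The size is uncertain. Across the scenarios, type I error runs from about 5.3% (ICC 0.01, regular attenders only) to about 12.8% (ICC 0.05, full circles, equal arms). Power at 308 runs from about 84% to 61%, against about 85% without clustering. The low end is minor and the high end is serious. The article gives no ICC with which to choose between them, so no single figure should be presented as the trial's error rate.

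**What to change.** In the Analysis plan, base inference for between-arm comparisons after baseline on one of two approaches:

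- a partially nested model with a random effect for circle in the PTSC arm only, usual-care women as singletons, arm-specific residual variance, and small-sample degrees of freedom (Satterthwaite or Kenward-Roger); or
- circle-robust standard errors with a small-sample correction.

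State a rule for circle membership. Use the assigned or chosen circle wherever one is recorded, whether or not the woman attended. Treat PTSC women who left before having a circle as singletons within the PTSC arm. The rule is needed because third-cohort women choose their circle, and the article does not say that membership is recorded for everyone.

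In the Power calculation, state the power for the planned size over an ICC range such as 0.01 to 0.05, without enrolling more women.

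The cost is a change of wording and a check that circle membership can be retrieved from programme records. Randomisation, intervention and outcome assessment are untouched. Intervals become somewhat wider and the stated power is lower than without clustering.
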